
### Other study parameters

In order to assess whether the treatment groups are similar with respect to baseline characteristics, several patient characteristics, injury characteristics, details of the shared decision process, and treatment characteristics will be collected.

#### Patient characteristics

AgeGenderBMIASA gradeTobacco consumption at baselineCharlson Comorbidity Index (CCI) [44]Medication use prior to traumaFAC scoreKatz Index of Independence in Activities of Daily Living (KATZ-ADL score)

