## Background

Proximal femoral fractures are amongst the most common fractures in the elderly [1] with the incidence rate increasing with age. In the Netherlands 20,000 patients are admitted with a proximal femoral fracture to the hospital each year [2, 3]. This number is expected to rise because of our ageing society. Approximately 20% live in a nursing home prior to the fracture. Proximal femoral fractures result in activities of daily living (ADL) dependence and increased morbidity, strongly diminishes the patients’ (health-related) Quality of Life (QoL) and total health care costs [4–7].

A proximal femoral fracture is also strongly associated with mortality. Over 30% of patients die within the first year and 8–13.3% die within the first month [8–10]. Mortality is highest among elderly with both physical and cognitive comorbidities [9, 10]. A 36 and 55% mortality rate within 6 months after fracture has been reported for institutionalized patients and patients with advanced dementia, respectively [11, 12]. This shows that the hip fracture is merely a symptom of the frail status of these patients and the start of cascade breakdown at the end of life.

Operative treatment allows early mobilization, is effective in pain relief, and is believed to prevent secondary complications like pneumonia, urinary tract infection, and pressure sores. However, surgery will not prevent frail patients from developing aforementioned complications. Instead, patients may develop additional surgical complications like bleeding, infection, and non-union, necessitating further (operative) interventions [13]. Hospital admission after a proximal femoral fracture itself can provoke cognitive impairment or delirium in these patients who often live in delicate equipoise in an institutionalized setting.

Although surgery is considered a good analgesic option, it is not the only analgesic option. Moreover, surgery also has disadvantages. It is questionable whether surgery is beneficial in terms of quality of life and whether surgery is satisfactory for family and caretakers involved. The World Health Organization (WHO) definition for palliative care supports a holistic approach in facing life-threatening illness, which is a proximal femoral fracture in a frail elderly patient. Randomized trials comparing operative and nonoperative management in institutionalized elderly are scarce, due to ethical issues, and focus on mortality instead of quality of life.

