### Study design and setting

This study will be a two-arm non-randomized (observational) multicenter cohort study and an economic evaluation alongside. The study will be conducted with a non-inferior design. Relevant societies for surgery (Dutch Association of Surgery (NVvH), Dutch Association of Trauma Surgery (NVT), Dutch Orthopaedic Association (NOV), and Dutch Association of Orthopaedic Surgery (NVOT)), clinical geriatrics (Dutch Association of Clinical Geriatrics (NVKG)), elderly care (Association of Elderly Care Physicians (VERENSO)), the Dutch Patient Federation, and two committee members of the Dutch guideline for treatment of proximal femoral fractures are represented in the study team. Patients will be recruited from several hospitals throughout The Netherlands. The following 26 hospitals will participate: Albert Schweitzer Ziekenhuis, Alrijne Ziekenhuis, Amphia Ziekenhuis, Amsterdam UMC (location VUmc), Bernhoven, Catharina Ziekenhuis, Deventer Ziekenhuis, Dijklander Ziekenhuis (location Westfriesgasthuis), Dijklander Ziekenhuis (location Waterland Ziekenhuis), Elisabeth TweeSteden Ziekenhuis, Erasmus MC, Flevo Ziekenhuis, Isala, Maasstad Ziekenhuis, Meander MC, Noordwest Ziekenhuisgroep, OLVG, Radboud UMC, Rijnstate, Rode Kruis Ziekenhuis, St. Antonius Ziekenhuis, Streekziekenhuis Koningin Beatrix, Tergooi, Ziekenhuis Gelderse Vallei, Ziekenhuis Tjongerschans, and Zorggroep Twente.

The study has started in September 2018. The recruitment period will be 24 months, with a follow-up of 6 months. The results of the study are expected mid-2021.

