## Discussion

Treatment guidelines for proximal femoral fractures are mainly focused on regaining function and independence in activities of daily living. Other considerations may apply to frail elderly with a limited life expectancy, for whom comfort and pain are particularly relevant. Whether or not operative treatment is needed in this respect is undecided. This study aims to investigate the value of nonoperative management versus operative management of proximal femoral fractures in a selected group of frail institutionalized elderly with a limited life expectancy.

There are some limitations to this study. First, selection bias could be a factor in this study, since patient or proxy opting for nonoperative management may arguably be in worse condition with regards to their pre-trauma condition and comorbidities. A randomized controlled trial (RCT) would have avoided selection bias, however randomizing patients with a limited life expectancy was considered unfeasible (and unethical) by the research team. Patient recruitment in trials randomizing between operative and nonoperative treatment is known to be challenging, and would likely introduce an unacceptably high level of selection bias; surgeons with clear preference for a particular treatment may be unwilling to inform patients about the study, and patients (or their proxy if patient is unable to decide) with preference for a particular treatment will not sign informed consent. The chosen observational design allows all centers and all patients to participate, and real-life data will be collected. For patients with severe cognitive impairment, informed consent will be obtained by their health care proxy. That makes the current study design the most feasible to investigate this issue. As a second limitation, it could be argued that the questionnaire completed by proxy may differ from the patients rating, however since the majority of this study population is expected to suffer from cognitive impairment, questionnaire completion by proxy will be inevitable. Finally, at least 26 hospitals will participate, and treatment protocol and shared decision processes may vary across sites. This may introduce some heterogeneity, but also makes the results more generalizable.

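### The baseline list has no explicit measure of cognitive status or dementia severity, so comparison of the non-randomized arms and adjustment on this confounder are inadequate as planned

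*Protocol article*

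**What the plan says.** Study design and setting describes a "two-arm non-randomized (observational) multicenter cohort study", with treatment settled by a structured shared decision. Other study parameters gives the purpose of the baseline data: "In order to assess whether the treatment groups are similar with respect to baseline characteristics". The list under Patient characteristics then names age, gender, BMI, ASA grade, tobacco, Charlson Comorbidity Index (CCI) and, at its end, "Medication use prior to traumaFAC scoreKatz Index of Independence in Activities of Daily Living". The injury, decision-process and treatment lists that follow add no cognitive item, and no row of Table 1 does so.

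Elsewhere the protocol gives cognition weight. The Background states: "Mortality is highest among elderly with both physical and cognitive comorbidities". It goes on: "A 36 and 55% mortality rate within 6 months after fracture has been reported for institutionalized patients and patients with advanced dementia". The Discussion says that "the majority of this study population is expected to suffer from cognitive impairment", and accepts as its first limitation that patients treated nonoperatively "may arguably be in worse condition with regards to their pre-trauma condition and comorbidities". The Statistical analysis section corrects the models for baseline differences and for center, without naming the covariates.

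**The concern.** A variable confounds this comparison if it influences both the choice of treatment and the outcome. The protocol itself links cognitive comorbidity to mortality. It is also plausible that dementia severity affects the choice between surgery and comfort-directed care, and the quality-of-life and pain scores. Correction for baseline differences can use only what has been recorded.

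The physical side of frailty is well covered by BMI, ASA, FAC and Katz. The cognitive side, which the Background names alongside it, has no dedicated item. If the arms differ in dementia severity, part of any difference in EQ-5D, QUALIDEM, pain or mortality may reflect that imbalance, and the planned data give only indirect means of detecting or removing it.

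**Working it through.** The protocol states no figure on this point, so there is nothing to reproduce. The check is a reading of the lists, followed by an illustration of scale.

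**1. What could carry cognitive information**

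| Recorded item | Where | What it offers |
|---|---|---|
| CCI | Patient characteristics | Possibly dementia as yes/no; the article does not list the items or say whether they are kept separately; no severity |
| Katz ADL | Patient characteristics | Functional dependence, from physical or cognitive causes |
| Pre-trauma QUALIDEM and EQ-5D | Table 1, note a | Quality of life, asked retrospectively at the 7-day visit, after the treatment decision |
| Participants in the decision | Details of shared decision process | Weak marker; relatives or a legal representative take part in any case |
| Patient or proxy completion of EQ-5D | Table 1 footnote | Weak marker; the proxy completes it, and the patient also where able |

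None of these measures cognition or stages dementia. A yes/no flag also separates patients poorly when most are expected to be impaired, and the Background's higher mortality figure is for advanced dementia, which is a distinction of severity.

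**2. Illustration for mortality**

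Inputs: 55% (advanced dementia) and 36% (institutionalized patients) at six months, from the Background. The imbalance between arms is assumed, because the protocol gives none.

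Shift = imbalance × (0.55 − 0.36) = imbalance × 0.19

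- 10 points: 0.10 × 0.19 = 0.019
- 20 points: 0.20 × 0.19 = 0.038
- 30 points: 0.30 × 0.19 = 0.057
- 40 points: 0.40 × 0.19 = 0.076

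The range is 1.9 to 7.6 percentage points, before any adjustment.

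**3. Illustration for the primary outcome**

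The protocol gives no effect of dementia on EQ-5D. Assume 0.05 to 0.30 points and the same imbalances, and compare with the non-inferiority margin of 0.15.

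- Smallest: 0.10 × 0.05 = 0.005, and 0.005 / 0.15 = 3% of the margin
- Largest: 0.40 × 0.30 = 0.12, and 0.12 / 0.15 = 80% of the margin

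The bias could be trivial or nearly as large as the margin. The document does not allow the range to be narrowed.

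**The case against.** The strongest reply has four parts.

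*The CCI is collected.* The Background itself treats cognition as a comorbidity, so the index may hold a dementia diagnosis. This stands. A reader might infer that no cognitive information is recorded at all, or that no model could adjust for it. The document does not support that: if CCI items are kept separately, a diagnosis may be recoverable, and Katz, pre-trauma QUALIDEM and pre-trauma EQ-5D would absorb part of the confounding. What remains uncovered is severity.

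*This is a condensed article.* The full protocol and case report form are not shown and may hold more, so it cannot be said that the data will not exist. That caution stands. But the list is itemised down to tobacco use, affected side and the name of the surgeon, and its stated purpose is to compare the arms. Leaving cognition out of a list that detailed is a weakness in what the document fixes, and not merely detail left for elsewhere.

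*Selection is acknowledged.* The Discussion concedes it and the models correct for baseline differences. Acknowledging the problem does not supply the variable that the correction needs.

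*The mortality arithmetic is fragile.* This also stands. A reader might take the shift as a lower bound, since the 36% group is not stated to be free of dementia. That does not follow: the two rates carry separate citations, nothing shows the populations to be comparable, and the shift ignores whatever CCI, ASA, FAC and Katz already absorb.

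**Conclusion.** The point holds in this form: the baseline list and Table 1 contain no explicit measure of cognitive status or dementia severity. Because treatment is chosen, the protocol links cognition to mortality, and impairment is expected in the majority, comparison and adjustment on this factor are inadequate as planned. They are not impossible, because partial surrogates exist.

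The size is unknown. The 1.9 to 7.6 point mortality shift and the 3% to 80% of the EQ-5D margin rest on assumed imbalances. The first also borrows two rates from different sources, and the second assumes the dementia effect as well. They show only that the issue could matter. That dementia severity influences treatment choice is plausible but not shown; the Discussion speaks of pre-trauma condition and comorbidities in general. This should be corrected, but it does not by itself invalidate the study.

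**What to change.** Add pre-trauma dementia diagnosis and recorded severity stage to Patient characteristics and to the Baseline Data row of Table 1. Abstract both from the medical files already used for baseline data, including the nursing-home file where available. Because the information is pre-trauma and comes from records, it can also be collected for patients already enrolled since September 2018.

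Report it by arm. Name it as a prespecified covariate in the EQ-5D, QUALIDEM, pain and mortality models. Code it sparingly, for example none/mild versus moderate/severe: the sample size section plans for only about 50 evaluable patients per arm, and the models already correct for center across 26 hospitals. Two levels cost one degree of freedom; a four-level stage would cost three.

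The cost is one abstracted field and no patient test. The downsides are some misclassification, because staging in records is uneven, so residual confounding will remain, and the loss of one or a few degrees of freedom.

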#### Injury characteristics

Affected sideType of fractureAdditional injuries

#### Details of shared decision process

Participants in processTreatment goals of each participating partyRelevant details of shared decision process

#### Treatment characteristics

Hospital admissionSurgical delayName of surgeonPrimary and secondary surgeon (resident or staff surgeon)Duration of surgeryType of anesthesiaPeripheral nerve blockDetails of nonoperative treatmentType of implant usedPeroperative complicationsMobilization ordersAnti-decubitus mattress

### Recruitment and informed consent

Eligible persons presented to the Emergency Department (ED) with a proven proximal femoral fracture will be informed about the study in the ED or upon admission at the surgical or geriatric ward. After an explanation of the study, they will receive written information and a consent form from the attending physician, the clinical investigator, or a research assistant. Patients meeting all inclusion criteria and none of the exclusion criteria will be recruited in the hospital within 48 h after hospital admission. Should patients not be able to sign informed consent themselves, a legal representative (proxy) will receive verbal and written information about the study by the attending physician, the clinical investigator, or a research assistant, and will be asked to consent with participation of the patient. After signing informed consent by patient or proxy, the shared decision process will be carried out using a structured approach. This will result in identifying the primary treatment that is deemed best for the individual patient. Participation in this study is on a voluntary basis. If patients (or proxy on their behalf) do not wish to participate, they can do so without specifying why. Deciding not to participate in the study will not affect regular treatment and follow-up care. Participants are allowed to withdraw from the study at any time after they have given their written consent.

### Study procedures and follow-up

Patients will be followed until 6 months after trauma or until death, whichever comes first. In addition, at the 6-month follow-up contact, the researcher or research assistant will document any secondary intervention that may be planned for the patient. A schedule of events is shown in Table 1. A flow chart is shown in Fig. 1.

**Table 1 Tab1:** Schedule of events and follow-up

Radiographs & Event forms	Screening	Enrolment	7 days (4–10 days)	14 days (11–17 days)	30 days (23–37 days)	3 months (11–15 weeks)	6 months (6–7 months)
X-ray or CT-scan	X						
Screening	X						
Informed Consent		X					
Shared Decision		X					
Baseline Data			X				
General Clinical FU			X	X	X	X	X
QoL (EQ-5D and QUALIDEM)			X^a^	X	X	X	X
PACSLAC and Analgesic use			X^a^	X	X	X	X
Complications and mortality			X	X	X	X	X
(Secondary) Interventions			X	X	X	X	X
Satisfaction of patient (or proxy)			X^b^	X^b^	X^b^	X^b^	X
QODD			X^b^	X^b^	X^b^	X^b^	X^b^
Satisfaction of caregiver			X^b^	X^b^	X^b^	X^b^	X
Health Care Use			X^a^	X	X	X	X
Early Withdrawal			^c^	^c^	^c^	^c^	^c^

EQ-5D is completed by proxy and (if possible) by patients themselves

^a^Asking for current and pre-trauma status; ^b^Only if patients died prior to that follow-up moment; ^c^Only if applicable

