**Fig. 1 Fig1:**
[figure not shown]
Flow of participants through the study

Following enrolment, treatment (either nonoperative or operative management) will be decided using a shared decision approach as mentioned above. Data will be acquired at 7, 14, and 30 days, and at 3 and 6 months after trauma.

Baseline data will be collected from the patient’s medical files or by interviewing the patient as soon as possible, but no later than at the visit after enrolment. At each follow-up visit, the coordinating researcher or research assistant will visit the patient. He will ascertain patient status (i.e., treatment details including analgesics and other health care use, mobility of the patients, adverse events/complications, secondary interventions, and will verify information within medical records). At each visit patients (or proxy) will be asked to complete a questionnaire for the EQ-5D. At those visits, a caregiver will be asked to complete the QUALIDEM and PACSLAC-D.

At the final visit at 6 months, patients (or proxy) and caregiver will be asked to complete a questionnaire relating to their satisfaction with the treatment approach. In case a patient has died during follow-up, his/her relatives and caregiver will be asked to complete this questionnaire. In addition, relatives will be invited for an interview to complete the QODD questionnaire. An early withdrawal form will be completed if patients (or proxy) decide to withdraw from the study.

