Multivariable analysis for continuous outcome measures that are repeatedly measured over time will be done using generalized estimating equations (GEE) for longitudinal analysis on a per-protocol and intention-to-treat basis to investigate the effect of treatment. In the primary GEE model, the primary outcome variable studied (quality of life on EQ-5D) will be analyzed as a dependent variable, using treatment (nonoperative versus operative) as between subjects variable and time as within subjects variable. The interaction term of group and time (group x time) will be assessed, to evaluate whether the change over time differed between groups. Analyses will be corrected for baseline differences and all models will be corrected for center of inclusion. Repeatedly measured continuous secondary outcome variables will be analyzed using similar GEE models. Continuous outcome measures only ones and dichotomous secondary outcome measures will be analyzed using multivariable linear regression models and logistic regression models, respectively.

Subgroup analysis are planned for patients with an intracapsular or extracapsular fracture.

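### Pre-trauma EQ-5D is first asked at the 7-day visit, after the treatment decision, so the recalled baseline can differ by arm and be carried into the adjusted contrast

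*Protocol article*

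**What the plan says.** In Table 1 (Study procedures and follow-up) the row for EQ-5D and QUALIDEM is empty at Screening and Enrolment. Its first mark is in the 7-day column, whose window is day 4 to 10, and it carries the footnote "Asking for current and pre-trauma status". Visits are counted from the injury: "Data will be acquired at 7, 14, and 30 days, and at 3 and 6 months after trauma". Informed consent and the shared decision are both in the Enrolment column. A note under the table says that a proxy completes the EQ-5D, and the patient too where possible.

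Recruitment and informed consent says that patients are "recruited in the hospital within 48 h after hospital admission", and that the structured decision process follows the signing of consent.

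The text after Fig. 1 says that baseline data come from medical files or a patient interview "as soon as possible, but no later than at the visit after enrolment". The same text ties the EQ-5D to the follow-up visits.

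Statistical analysis states: "Analyses will be corrected for baseline differences". It does not name the covariates.

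**The concern.** The design is observational. The Discussion expects that those who opt for nonoperative care may be in worse pre-trauma condition, so the primary comparison depends on how well the arms are equalised at entry. For an EQ-5D outcome, the pre-trauma EQ-5D is the natural covariate, although the article does not say so.

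As scheduled, that covariate is measured after the exposure. The respondent gives the current and the pre-trauma state at the same visit, knowing which treatment was chosen and how its first days went. If this colours recall differently in the two arms, correcting for the recalled score introduces a difference that did not exist before the fracture.

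A lesser matter is that patients who die before the visit have no scheduled pre-trauma score, and early death may well be more frequent in one arm.

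**Working it through.** **1. Order of events, from Table 1 and the text**

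| Event | Timing |
|---|---|
| Consent, then shared decision | Enrolment, within 48 h of admission |
| Treatment | After the shared decision |
| First EQ-5D, current and pre-trauma | 7-day visit, day 4–10 after trauma |
| Other baseline data | As early as possible, at the latest the first visit |

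The allowance for earlier baseline collection does not reach the EQ-5D. It refers to files and patient interview, the EQ-5D is described separately as part of the follow-up visits, and it is not in the lists under Other study parameters. There is an edge case: only fractures diagnosed more than 7 days after trauma are excluded, so a late-diagnosed patient may reach the day 4–10 window at or before treatment. Hence treatment has usually, not always, begun.

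**2. How differential recall enters the contrast**

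With Y the outcome, X the recalled baseline and b the slope of Y on X, the adjusted contrast (operative minus nonoperative) is

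(Ȳ_op − Ȳ_non) − b × (X̄_op − X̄_non).

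If nonoperative respondents recall X too low by d relative to operative respondents, the contrast falls by b × d, which favours nonoperative care. If the recall error has the opposite sign, the contrast rises by the same amount. The documents give neither b, nor d, nor the sign, so the route can be shown but not the size.

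**3. Patients without a scheduled pre-trauma score**

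Inputs from Background: 30-day mortality of 8–13.3% in hip fracture generally, and an unadjusted 30-day odds ratio of 3.95 for nonoperative versus operative management. Assumptions: the 8–13.3% is the operative rate, and the hazard is constant over 30 days.

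Nonoperative 30-day mortality:
- 0.08/0.92 × 3.95 = 0.343 odds, so 0.343/1.343 = 25.6%
- 0.133/0.867 × 3.95 = 0.606 odds, so 0.606/1.606 = 37.7%

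Deaths by day t = 1 − (1 − p)^(t/30):

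| Day | Operative (p = 8% to 13.3%) | Nonoperative (p = 25.6% to 37.7%) |
|---|---|---|
| 4 | 1.1–1.9% | 3.9–6.1% |
| 7 | 1.9–3.3% | 6.7–10.5% |
| 10 | 2.7–4.7% | 9.4–14.6% |

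If the planned 160 split evenly (assumption), the day-7 row is about 1.5–2.6 of 80 operative and 5.3–8.4 of 80 nonoperative patients, roughly 1 to 3. Deaths concentrated in the first days would raise both figures.

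**4. Where those gaps matter**

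A patient who dies before the first visit has no follow-up EQ-5D either, and so supplies no observed outcome to the GEE or the 6-month contrast. What is lost is a pre-trauma score for comparing the arms at entry and for informing imputation.

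**The case against.** Several points on the other side stand.

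- **Coloured recall is a risk, not a shown fact.** Nothing in the article demonstrates it. A reader might attach a size, for example a recall difference of 0.05 with a slope of 0.5, which moves the contrast by 0.05 × 0.5 = 0.025, or 17% of the 0.15 margin. Neither input has a source in the documents, so that figure is not evidence of the harm.
- **Early deaths barely touch the primary analysis.** A reader might infer that their missing baselines weaken the adjustment. They do not, for the reason in step 4 of the working.
- **The source is not lost at death.** Table 1 has relatives approached about satisfaction and quality of dying, from the 7-day column onward. They could be asked about the pre-trauma state, but the plan does not schedule it.
- **The QALY effect is negligible.** Seven days is 7/365 = 0.019 year. A utility error of 0.30 (the planning SD) changes one early decedent's QALY by 0.019 × 0.30 ≈ 0.006, and with 8 such deaths among 80 (assumed) the arm mean moves by about 0.0006.
- **Other covariates exist.** Age, BMI, ASA, Charlson index, FAC and KATZ-ADL are collected, and several do not rest on recalled quality of life. That pre-trauma EQ-5D will be a covariate is an inference.
- **Asking at consent is not perfect.** The score is still recalled, in an acute situation, and asking just before the decision might influence it.

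The Discussion acknowledges selection and the possible difference between proxy and patient ratings. It does not address when the pre-trauma score is asked. None of these points gives a reason for asking it after the treatment decision when the patient or proxy is already seen before it.

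**Conclusion.** The point holds as one about timing. The only scheduled pre-trauma EQ-5D is taken after the treatment decision, usually after treatment has begun, and from unblinded respondents who report the current state at the same visit. In a non-randomized comparison that is to be corrected for baseline differences, such a covariate can carry a difference in recall into the non-inferiority contrast, in either direction. The size cannot be derived from the documents.

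The missing scores are secondary: about 2–3% operative against 7–10% nonoperative by day 7. That is an illustration resting on a constant hazard, a general hip-fracture mortality taken as the operative rate, and an unadjusted odds ratio. The documents do not support reading it as a bias in the primary contrast or as a material QALY error. The change is worth making because it is cheap and a score not taken before the decision cannot be recovered later.

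**What to change.** In Table 1, add the pre-trauma EQ-5D to the Enrolment column (proxy version, plus the patient version if able), to be completed at consent and before the shared decision. Keep the 7-day visit for current status. State in Statistical analysis that the enrolment value is used for the baseline comparison and as the baseline EQ-5D covariate in the adjusted models. It should not serve as the starting value for the QALY, because it describes health before the fracture.

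QUALIDEM and PACSLAC can stay where they are: a caregiver completes them, who need not be present at hospital consent.

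The cost is a schedule amendment, a five-item form at a contact that already takes place, and a small burden on relatives in the acute phase. The score remains a recalled one, but it is recalled before the treatment decision. The study has already started, so for participants enrolled before the amendment only the 7-day recall will exist, and the report should say which timing applies to whom.
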